## Abstract

**Background:**

Many candidate vaccine strategies against human immunodeficiency virus (HIV) infection are under study, but their clinical development is lengthy and iterative. To accelerate HIV vaccine development optimised trial designs are needed. We propose a randomised multi-arm phase I/II design for early stage development of several vaccine strategies, aiming at rapidly discarding those that are unsafe or non-immunogenic.

**Methods:**

We explored early stage designs to evaluate both the safety and the immunogenicity of four heterologous prime-boost HIV vaccine strategies in parallel. One of the vaccines used as a prime and boost in the different strategies (vaccine 1) has yet to be tested in humans, thus requiring a phase I safety evaluation. However, its toxicity risk is considered minimal based on data from similar vaccines. We newly adapted a randomised phase II trial by integrating an early safety decision rule, emulating that of a phase I study. We evaluated the operating characteristics of the proposed design in simulation studies with either a fixed-sample frequentist or a continuous Bayesian safety decision rule and projected timelines for the trial.

**Results:**

We propose a randomised four-arm phase I/II design with two independent binary endpoints for safety and immunogenicity. Immunogenicity evaluation at trial end is based on a single-stage Fleming design per arm, comparing the observed proportion of responders in an immunogenicity screening assay to an unacceptably low proportion, without direct comparisons between arms. Randomisation limits heterogeneity in volunteer characteristics between arms. To avoid exposure of additional participants to an unsafe vaccine during the vaccine boost phase, an early safety decision rule is imposed on the arm starting with vaccine 1 injections. In simulations of the design with either decision rule, the risks of erroneous conclusions were controlled <15%. Flexibility in trial conduct is greater with the continuous Bayesian rule. A 12-month gain in timelines is expected by this optimised design. Other existing designs such as bivariate or seamless phase I/II designs did not offer a clear-cut alternative.

**Conclusions:**

By combining phase I and phase II evaluations in a multi-arm trial, the proposed optimised design allows for accelerating early stage clinical development of HIV vaccine strategies.

## Background

Although several promising approaches to prevent human immunodeficiency virus (HIV) infection have been put forth in the recent years [1-4], the development of a prophylactic vaccine strategy remains a key goal in the effort to end the HIV epidemic.

The main prophylactic HIV vaccine candidates currently under study include subunit or epitope-based vaccines with or without adjuvants, recombinant virus-vector vaccines and deoxyribonucleic acid (DNA) vaccines. The combination of different vaccines into heterologous prime-boost strategies is today considered a promising approach. Indeed, results of a phase IIB trial in Thailand (RV144 trial), combining a virus-vector vaccine prime with a subunit boost, showed a modest protective effect of the tested HIV vaccine strategy [5]. HIV vaccine development remains ongoing and too lengthy. For instance, clinical development of the components of the HIV vaccine strategy evaluated in the RV144 trial started in the mid-1990s in Thailand, however the results of the aforementioned phase IIB trial only became available in 2009. According to development timelines, a confirmatory phase III trial with an improved vaccine strategy is not projected to start before 2019 [6,7].

The fact that immunological correlates of protection are not well understood has hampered HIV vaccine development to date [8]. A protective vaccine effect can currently not be predicted on the basis of vaccine-induced immunogenicity markers. Since transition from phase I/II to phase IIB/III trials can thus not rely on a validated surrogate immunogenicity endpoint, and large sample sizes and resources are required for later-stage trials with HIV-acquisition endpoints (phase IIB/III), the clinical development of HIV candidate vaccine strategies is laborious. Phase I and II HIV vaccine trials usually include extensive immunogenicity assessments, measuring both the humoral and cellular immune responses to vaccines with different markers and techniques. All of the above complicates the decision to set up a large-scale IIB/III trial, powered for an HIV-acquisition endpoint. These constraints have resulted in only six HIV vaccine phase IIB/III trials conducted so far, five of which yielded disappointing results without any evidence for protective vaccine effects [9-11].

Recently, calls for accelerated clinical development of HIV vaccine strategies have been put forward, advocating the implementation of adaptive trial designs for this purpose [12,13]. Indeed, numerous adaptive or multi-stage clinical trial designs for different phases of clinical development are available in the methodological literature. However, these designs were mainly devised for cancer treatment trials, which differ from HIV vaccine trials. In oncology, the patients who are enrolled in trials suffer severe illness requiring treatment. Inefficacious strategies must thus be identified as soon as possible to avoid harm. In contrast to oncology trials, including trials for therapeutic cancer vaccines [14], the development of prophylactic HIV vaccines targets a non-ill population and thus necessitates specific design considerations. Moreover, assessment of endpoints is clearer in oncology trials both because of a higher incidence and more well-defined surrogate endpoints, such as tumour response criteria [15]. The application of adaptive trial designs to HIV vaccine research is challenging given that numerous immunogenicity endpoints without a definite hierarchy are evaluated in phase II trials and that clinical development plans should remain flexible enough to accommodate new scientific knowledge. Thus, trial design optimisation has rarely been considered in HIV vaccine research, yet as the number of potential HIV vaccine strategies under development increases it has become of greater interest [16]. Gilbert et al. proposed an adaptive phase IIB/III design with an HIV-acquisition endpoint for mid- to late-stage clinical development (phase IIB/III), which has yet to be applied in practice [17]. For early-stage development, Moodie et al. recommended a phase IB selection design in 2006 to prioritise among different candidate vaccine strategies the one with the top-rank based on an immunogenicity endpoint. At that time, they considered that knowledge about HIV vaccine immunogenicity was too limited to select vaccine strategies using bounds based on a theoretical response rate [18]. To date, although understanding of vaccine-elicited immune responses still requires much more progress, this justification has evolved. We now consider it purposeful to define an insufficient response level in a widely used, validated immunogenicity screening assay [19].

Currently, more than 20 ‘generic’ HIV candidate vaccines are in early clinical development [16]. Given that generic candidates may be tested with different antigen inserts, that combinations of different candidate vaccines are evaluated and that strategies with the same combination may differ in terms of the timing of injections, the number of potential vaccine strategies is large. Efficient screening of potential strategies and decision making in early stage development is thus crucial. In the present article, we present an early-stage trial design, integrating phases I and II to evaluate both safety and immunogenicity endpoints of several HIV vaccine strategies in parallel and allowing for the rapid cessation of those with insufficient safety or immunogenicity levels.

## Methods

### Motivating example

Our search for an optimised phase I/II HIV vaccine trial design was motivated by the clinical development plan of a vaccine portfolio comprising three prophylactic HIV candidate vaccines, referred to herein as ‘vaccine 1’, ‘2’ and ‘3’.

Vaccine 1 is a viral vector (modified vaccinia Ankara (MVA) virus) expressing HIV antigens, which has not yet been evaluated in humans with the specific HIV inserts used. It therefore requires a phase I safety study before it can be administered to a larger number of volunteers. However, the MVA vector with different HIV and non-HIV inserts has already been studied in previous trials and has a good safety profile in humans [20-26]. Minimal toxicity is thus expected for vaccine 1. The tested target dose (1x10^8^ plaque-forming units) corresponds to the standard dose tested for MVA vaccinations against smallpox [22,27] and to the dose selected in previous dose-escalation studies of MVA vectors with HIV and non-HIV inserts [20,24,28,29]. No dose escalation is thus planned for this vaccine in our development plan.

Vaccine 2 is a lipopeptide vaccine, including an equal-weight mix of five synthetic HIV-1 peptides coupled to a palmytoil tail (HIV LIPO-5). Vaccine 3 is a deoxyribonucleic acid (DNA) vaccine, encoding for a multi-HIV antigen. Both vaccines 2 and 3 have been studied previously in phase I and II trials and have a good safety record [30-33].

In the clinical development plan of this vaccine portfolio, the three vaccines are combined into four heterologous (that is, using different vaccines in the prime and the boost phase) prime-boost strategies (Figure 1). Vaccine 3 is currently being considered only for use as a prime vaccine component, and not as a boost [34].

**Figure 1 F1:**
[figure not shown]
**Overview of the proposed multi-arm phase I/II design.** Legend: W = week.

In our clinical development plan, the aim of the phase I evaluation of vaccine 1 at the target dose is to stop administrations of this vaccine as soon as possible in case of a safety problem. The early stage of the phase II evaluation aims at screening each of the four prime-boost combinations for a minimum immunogenicity level. Non-immunogenic or unsafe vaccine strategies should be discarded as soon as possible. A ‘classical’ clinical development scheme with several phase I and II trials to address these objectives would be a lengthy process. In order to accelerate the clinical development and given the high likelihood of a good safety profile of vaccine 1 similar to the one observed with different HIV inserts, we sought to set up an optimised trial design combining phases I and II for evaluation of the four prime-boost strategies in parallel.

For the purpose of the present work, we defined an ‘optimised design’ as a trial design allowing for a gain in timelines (and, if possible, in the number of trial participants) compared to separate phase I and II trials, while remaining feasible and respecting the requirements outlined below.

### Requirements for the optimised phase I/II vaccine trial design

In searching for an optimised design appropriate for our development plan, we imposed the following methodological requirements:

• First, a randomised multiple arm design is desirable to ensure comparability of populations and unbiased assessment of several vaccine strategies in parallel, even if no direct statistical comparisons are made between arms [35].

• Second, the design requires an evaluation of both immunogenicity and safety endpoints, assessed at different time points, allowing for an early safety decision rule to emulate the phase I evaluation of vaccine 1 during the vaccine prime phase. The dose used for vaccine 1 is considered well below the toxic dose.

• Third, endpoints for immunogenicity and safety are not necessarily correlated, since severe vaccine-related toxicity events and immunogenicity are likely to be unrelated [36].

• Fourth, an important constraint of the design is the fact that safety and immunogenicity outcomes are not observed simultaneously, since the immunogenicity measurements of all participants are planned in batch at a central laboratory at the end of the trial to allow for blinded assessments and to limit measurement error due to time and batch effects.

• Fifth, data integration of phase I into phase II evaluation should be possible to allow for an optimal use of the collected data.

• Sixth, the trial design must be compatible with high early accrual dynamics and with conduct as a multi-centre trial. Prophylactic HIV vaccine trials enrol healthy volunteers, a process that allows for better planning and management of recruitment dynamics than the enrolment of ill patients. To keep costs low, a single call for volunteers is planned for our trial. As previous vaccine trial recruitment studies have shown that a ‘waiting time’ between the first contact and enrolment may lead to a loss of interest in participation [37], the time between the call for volunteers and the start of the trial will be kept short. Altogether, this is expected to result in high early accrual dynamics.

• Lastly, a design without a control group was favoured since HIV-specific immune responses can be considered to be close to zero in healthy volunteers at low risk of HIV infection, as attested by immune response measurements in prophylactic HIV vaccine trials at baseline or in a placebo arm [20,21,38-40]. A vaccine strategy meeting the immunogenicity endpoint can therefore be deemed clearly distinct from a potential control group. Given that the volunteers in the planned trial will have a low-risk profile (restricted by the eligibility criteria) and the fact that all participants will receive an experimental vaccine strategy, we considered it unlikely that differential risk behaviour during the trial would have an impact on the immunogenicity endpoint.

A summary of these requirements is shown in the list below:

▪ randomized multi-arm trial

▪ evaluation of both efficacy and safety endpoints, with:

– early safety decision rule

– difference in timing of the evaluation between the two endpoints

– assumption that toxicity events and efficacy are likely unrelated

– efficacy outcome not observed in real-time (measured in batch in central lab at end of the trial)

– data integration of phase I into phase II efficacy evaluation

▪ compatibility with high early accrual dynamics and with conduct as a multi-centre trial

▪ no control arm

Moreover, although not a formal design requirement, an open-label design was preferred since the immunogenicity endpoint can be measured objectively and laboratory staff performing the measurements centrally will be blinded to trial arm and time point. Although a blinded control group would limit bias in the evaluation of safety, implementation of blinding is difficult in practice: indeed, blinding would require the introduction of dummy vaccine injections in each trial arm, since vaccination time points during the prime phase vary between vaccine strategies (Figure 1). Additional immunogenicity sampling time points after each dummy shot would then be necessary for maintaining blinding, requiring large amounts of blood. Blinding participants and site staff was thus not pursued for this trial design, but we acknowledge that a blinded placebo control arm could be helpful for safety assessments when feasible.

### Search for the optimised design

We first searched the literature for existing trial designs fulfilling the requirements outlined above in order to be appropriate for application to early stage clinical HIV vaccine development. We performed a literature search in Pubmed/Medline using the search terms (‘Clinical Trials, Phase II as Topic’ [MAJR]) AND (‘Therapeutics/adverse effects’ [MeSH] OR safety OR toxicity). In addition, the review and manual of phase II designs by Brown et al. were used to identify potential designs for our context [41]. Moreover, we reviewed the reference lists of the most relevant articles.

We then adapted a randomised phase II design to include an early safety decision rule during the prime phase of vaccine 1. We evaluated two types of statistical approaches for the safety decision rule: (1) a fixed-sample rule from a frequentist perspective; and (2) a continuous safety monitoring approach from a Bayesian perspective. Simulation studies were built to evaluate the statistical properties of the design with either decision rule. For each simulation scenario under different underlying safety and immunogenicity hypotheses, the participant outcomes for a trial arm with a safety decision rule (arm 1 in our trial design) were drawn from independent binomial distributions of the binary safety and immunogenicity endpoints respectively, and repeated in 10,000 simulation runs. We also performed ancillary simulation studies based on draws of participant outcomes from multinomial distributions, with specified joint probabilities of the two endpoints (corresponding to positive correlations from 0.1 to 0.5 between immunogenicity response and occurrence of vaccine-related toxicity events) [42], while keeping the marginal proportions of the endpoints constant. Recruitment dynamics were not taken into account for the simulation studies. Simulations were performed with R software, version 2.13.0 (The R Foundation, Vienna, Austria).

Furthermore, we projected the expected dynamics of recruitment into the trial and the gain in timelines of the clinical development plan by the proposed design based on our previous experience setting up and conducting HIV vaccine trials in France [32,43,44].

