Each arm of the phase II design has a single-stage Fleming design for the binary immunogenicity endpoint [48], comparing the proportion *P* of participants with a positive IFN-γ ELISPOT response to a theoretical unacceptable proportion of 50%. The randomised design with parallel arms is thus not intended for formal between-arm comparisons but to limit heterogeneity in volunteer characteristics between arms. In contrast with the randomised phase II selection designs used in oncology [14], this design does not aim to select one single strategy (that is, the ‘best’ strategy) at the end of the phase II design but retains all strategies with responses above a minimal level. The decision rule is formulated per arm and does not depend on the number of parallel arms in the trial, which distinguishes its operating characteristics from those of randomised phase II selection designs [49]. The sample size of n = 23 per arm was determined from published sample size tables based on exact binomial distributions, with 90% power, one-sided type I error rate of 5%, p1 of 80% (target proportion of IFN-γ ELISPOT responders), and p0 of 50% (unacceptably low proportion of IFN-γ ELISPOT responders) [50].

The integrated phase I evaluation of vaccine 1 is based on an independent binary safety endpoint at week 2 in arm 1, evaluating the proportion of participants without any grade 3 or 4 clinical or biological adverse events related to vaccine 1 immunisation, reported from week 0 to week 2. Event relatedness will be reviewed and grades validated by the Endpoint Review Committee.

We evaluated two types of safety decision rules, with the aim to avoid exposure of additional participants to an unsafe vaccine during the vaccine boost phase.

First, we considered a frequentist fixed-sample approach, which was also derived from a single-stage Fleming design, with 90% power, one-sided type I error rate of 5%, p1 of 95% (target proportion of participants without any vaccine-related adverse event), and p0 of 70% (unacceptably low proportion of participants without any vaccine-related adverse event). Based on the proportion at which the lower bound of the one-sided exact 95% confidence interval includes p0, this translates into the following safety decision rule for vaccine 1 [50]: if more than two out of the first 19 participants in arm 1 experience a vaccine-related adverse event by week 2, then all vaccine 1 injections will be stopped.

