Second, we studied a Bayesian sequential safety monitoring approach, allowing (1) for formally incorporating the previously available knowledge about the safety of MVA vectors in the prior distribution, and (2) for continuously updating the posterior distribution after each participant or observed event during the trial [51]. We used an enthusiastic prior distribution (Beta (6, 0.3)) to reflect the sound prior knowledge about the safety of this vector type. The Bayesian safety decision rule was then defined based on the posterior probability that the proportion of participants without any vaccine-related adverse event is below the target proportion of 0.95. At any sequential analysis, the injections of vaccine 1 would be stopped if this posterior probability was greater than 95% (Prob (Psafe < 0.95|data) > 0.95).

Given the planned rapid accrual dynamics of the trial, the proposed safety decision rules do not aim at halting enrolment, which may be completed before the decision rule applies. Thus, the decision rule is not necessarily expected to impact the number of volunteers enrolled. Rather, it aims at taking a go/no-go safety decision before the start of the vaccination boost phase at week 20 to avoid exposing additional participants to vaccine 1 in the other trial arms. If administrations of vaccine 1 are stopped, arms 1 and 2 are halted but arms 3 and 4 continue, with participants in arm 4 receiving boost injections of vaccine 2 instead of vaccine 1.

Simulation results for each of the two safety decision rules are shown in Table 1.

**Table 1 T1:** Comparison of operating characteristics of the two types of safety decision rules

**Type of safety decision rule**		**Simulation scenario**		
	**Vaccine safe (P**_ **safe** _ **= 0.95)**	**Vaccine unsafe (P**_ **safe** _ **= 0.7)**		
	**Probability of stopping**	**Probability of stopping**	**Participant number at stop (median; IQR)**	
Fixed-sample frequentist rule at n = 19	0.07	0.95	19	(19-19)^a^
Continuous Bayesian monitoring	0.05	0.96	8	(4-12)

Fixed-sample frequentist rule: Interim analysis after 19 participants. Vaccine considered unsafe at interim if lower bound of one-sided exact 95% confidence interval of observed proportion ≤0.7 for safety endpoint.

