^a^In a strict application of the fixed sample-design the decision rule only applies when the outcome of 19 participants has been observed. If the application of the rule was handled more flexibly (that is stopping as soon as a third participant experiences an vaccine-related grade 3 or 4 adverse event, regardless of the denominator), stopping would occur after nine participants in median (IQR 6-12).

Continuous Bayesian monitoring of the safety endpoint: Sequential analysis after each participant or event. Vaccine considered unsafe at the first analysis where the posterior probability that the vaccine is below the target level (Psafe <0.95) exceeds 95%. Enthusiastic prior: beta (6,0.3).

Table 2 summarises the combined operating characteristics of a trial arm in the final phase I/II design, including both the frequentist analysis of the immunogenicity endpoint at week 30 as well as the continuous Bayesian monitoring of the safety endpoint at week 2. The simulated operating characteristics were satisfactory under all combinations of the hypotheses for safety and immunogenicity respectively, with a maximum overall error rate of 12.1%.

**Table 2 T2:** Combined operating characteristics of the design including a frequentist efficacy evaluation and the continuous Bayesian safety decision rule

**Simulation scenario**		**Proportion of outcomes in 10,000 simulations of one trial arm (%)**			
**Safety hypothesis**	**Immunogenicity hypothesis**	**Vaccinations stopped (unsafe)**	**Vaccinations not stopped (safe), inefficacious at final**	**Vaccinations not stopped (safe), efficacious at final**	**Overall probability of erroneous conclusion**
Unsafe (0.70)	Inefficacious (0.50)	95.5	4.2	0.3	**4.5**
Unsafe (0.70)	Efficacious (0.80)	95.6	0.3	4.1	**4.7**
Safe (0.95)	Inefficacious (0.50)	4.8	91.4	3.8	**8.6**
Safe (0.95)	Efficacious (0.80)	5.3	6.8	87.9	**12.1**

Simulation methods: Simulation of independent binomial distributions for safety and efficacy, respectively. Simulation of participant outcomes for one trial arm with continuous Bayesian monitoring of the safety endpoint, repeated in 10,000 trial simulations per simulation scenario.

Bayesian continuous monitoring of the safety endpoint. Decision rule for safety outcome: Vaccine considered unsafe at the first analysis where the posterior probability that the vaccine is below the target level (Psafe <0.95) exceeds 95%. Enthusiastic prior: beta (6,0.3).

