Continuous toxicity monitoring approaches from the frequentist perspective, such as those suggested by Goldman et al., Kramar et al., Ivanova et al. or Ray et al. [42,55,56,62] require that the participants (or events) be observed sequentially (that is, one by one), which is not granted with high accrual dynamics. An alternative approach to Bayesian continuous safety monitoring could have been designed based on the predictive probability instead of the posterior distribution. In the context of efficacy monitoring with slightly higher maximum sample sizes than in our design it has been shown to have similar operating characteristics than the method based on the posterior distribution [63]. However, applying decision rules based on future probabilities to a safety endpoint is conceptually less intuitive, and we believe that a rule based on the current posterior distribution better resembles the decision making process for safety. For the same rationale, we did not pursue the approach published by Yu et al. who suggested toxicity monitoring based on a probabilistic approach estimating the future rate of toxicity [57].

Most existing bivariate two-stage designs for combined safety and efficacy evaluation, be they frequentist or Bayesian [53,64-67], were developed in the context of cytotoxic cancer drug development and generally require both the efficacy and the safety outcome to be observed and analysed with the same timing. This is not the case in our vaccine trial where the immunogenicity outcome is measured in batch at the end of the trial. Although a group-sequential bivariate design with increased flexibility, accommodating different schedules for efficacy and safety analyses was also suggested, this design still requires at least one analysis time including both safety and efficacy endpoints [68].

Lastly, we considered the seamless phase I/II frequentist design proposed by Messer et al. [54], the rationale of which is very close to ours. However, their design is appropriate for a single-arm trial, using a 3 + 3 enrolment scheme in phase I, but is too complex to implement in the context of a multi-center multi-arm trial and is not compatible with the accrual dynamics expected for the healthy volunteers in our trial. Other seamless phase I/II designs comprising a dose-finding phase have the same limitations for application in our context [69].

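### The Bayesian safety rule's 0.05 false-stop probability and 12.1% maximum error assume participants observed one by one; under the planned fast accrual they depend on an unstated counting convention

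*Protocol article*

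**What the plan says.** - **Simulation.** Under Search for the optimised design, arm 1 outcomes were drawn from independent binomial distributions, and "Recruitment dynamics were not taken into account for the simulation studies".
- **Prior and threshold.** Under Characteristics of the proposed optimised phase I/II design: "We used an enthusiastic prior distribution (Beta (6, 0.3)) to reflect the sound prior knowledge about the safety of this vector type". At any sequential analysis "the injections of vaccine 1 would be stopped if this posterior probability was greater than 95" per cent; this is the posterior probability that the event-free proportion lies below 0.95.
- **Timing of looks.** The approach is described as allowing "for continuously updating the posterior distribution after each participant or observed event during the trial". The note to Table 1 repeats it: "Sequential analysis after each participant or event", with the first crossing deciding.
- **Endpoint.** It is freedom from related grade 3 or 4 events between week 0 and week 2. Practical implications asks for real-time monitoring and validation of such events up to week 2.
- **Accrual.** The sixth requirement plans a single call for volunteers with a short wait: "Altogether, this is expected to result in high early accrual dynamics". The article adds that enrolment may be complete before the rule applies.
- **Alternatives.** In the text after Table 3, frequentist continuous approaches are ruled out because they "require that the participants (or events) be observed sequentially (that is, one by one), which is not granted with high accrual dynamics".
- **Results.** Table 1 gives stop probabilities of 0.05 (safe) and 0.96 (unsafe) and a median of 8 (IQR 4-12) participants at the stop. Table 2 gives a maximum error of 12.1%. The abstract reports all such risks as below 15%.

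**The concern.** The objection used to discard the frequentist rules applies equally to the Bayesian rule's published operating characteristics. A posterior can be calculated at any time, but the probability that it ever crosses 0.95 depends on the order in which data arrive. An event can be known on the day it occurs, whereas a non-event is known only when the two-week window closes. With rapid accrual, events can therefore reach the posterior ahead of the event-free participants enrolled alongside them. The boundary is steep at small numbers, so this ordering matters.

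A false stop is costly. Arms 1 and 2 are halted and arm 4 takes the arm 3 boost, which leaves one of the four strategies. The article also favours the Bayesian rule for its tolerance of departures from projected accrual, a property that the simulations did not test.

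**Working it through.** **Inputs.** Arm size 23 ("The sample size of n = 23 per arm was determined from published sample size tables"); prior Beta(6, 0.3); stop if Pr(Psafe < 0.95 | data) > 0.95; Psafe 0.95 (safe) or 0.70 (unsafe); immunogenicity success if the exact one-sided 95% lower bound exceeds 0.5, which means at least 16 of 23.

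**1. Boundary.** After x events among n counted participants the posterior is Beta(6 + n − x, 0.3 + x). With x = 2, Pr(Psafe < 0.95) is 0.975, 0.967, 0.958 and 0.9475 at n = 2, 3, 4 and 5. The rule therefore stops at 2 events for n up to 4, 3 events for n = 5-14, and 4 events for n = 15-23. Two events among all 23 give only 0.67.

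**2. The published figures.** An exact recursion over participants 1 to 23, each fully observed before the next, gives stop probabilities of 0.0497 (safe) and 0.955 (unsafe), with a median of 8 (IQR 4-12) at the stop when unsafe. This matches Table 1. For the safe and efficacious row, P(X ≥ 16 | 23, 0.80) = 0.9285, so

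overall error = 1 − (1 − s) × 0.9285,

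where s is the false-stop probability. With s = 0.0497 this is 11.8%, against 12.1% from the authors' simulation. The published figures are those of strict one-by-one observation.

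**3. Other orders of observation, Psafe = 0.95.** Calendar-time simulation. Where two values are given, event onset is uniform over 14 days / within days 0-3. The lag rows assume 92 participants (4 × 23) enrolled over all arms.

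| What enters the posterior | Assumed accrual | False stop |
|---|---|---|
| Completed week-2 windows, in enrolment order | any spread-out accrual | about 5% |
| Single look at all 23 | not applicable | 2.6% |
| Events, with all vaccinated arm 1 participants as denominator | any | about 2-5% |
| Events at onset, non-events at week 2 | 24-hour lag for first 20, then 2/day | about 7-9% |
| same | lag, then 5/day | about 10% / 14% |
| same | lag, then 10/day | about 11-18% |
| same, 3-day validation delay | lag, then 2-10/day | about 6-14% |
| same, no delay | no lag, arm 1 filled over 8 weeks | 7% / 9% |
| same, no delay | no lag, arm 1 filled over 4 weeks | 10% / 16% |
| same, no delay | no lag, arm 1 filled over 2 weeks | 16% / 30% |
| same, no delay | all of arm 1 pending at once | 32% |

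The last row is a ceiling. At least two events are needed to stop, so s cannot exceed P(X ≥ 2 | 23, 0.05) = 1 − 0.95²³ − 23 × 0.05 × 0.95²² = 1 − 0.3074 − 0.3721 = 0.32.

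**4. Effect on the overall error.** The 15% limit is passed when (1 − s) × 0.9285 < 0.85, that is, when s > 1 − 0.85/0.9285 = 0.0845. At s = 0.07 the error is 13.7%; at 0.18 it is 1 − 0.82 × 0.9285 = 23.9%; at the ceiling it is 36.9%.

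**5. Direction.** Detection at Psafe = 0.70 is not harmed. It is 0.94-0.96 with all vaccinated in the denominator, and at least 0.96 in the scenarios run with events entering at onset. The possible inflation lies in false stops.

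**The case against.** A reader might infer that the rule as stated gives 9-30% false stops. The article does not support that. Nowhere does it say that events count at onset while participants in progress are left out. It describes a binary endpoint at week 2, and note c to Table 3 places the safety evaluation there. Updating on completed windows in enrolment order keeps the rate at about 5%. The wording on looks after each participant or event permits the unfavourable reading but does not require it.

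Three further points reduce the size. An Endpoint Review Committee must judge relatedness and validate grades, so events are not counted instantly: with the lag and then 5 per day, a 7-day delay brings false stops to 4.9% / 8.3% (uniform / exponential onset with a mean of 2 days). Further perspectives describes the 24-hour lag, so the highest figures, which omit it, are not this trial's plan. The decision is also aimed at week 20, which leaves time for pending outcomes to arrive, although the rule as written stops at the first crossing.

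It is also fair that the omission of accrual is disclosed, and that the detail of who enters each look may sit in the full protocol. These points stand, and silence on that detail alone would not be a finding. They do not remove the inconsistency: error control is reported as a result of the design, and it was derived under an observation order that the article says fast accrual does not grant.

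**Conclusion.** The point holds in conditional form. The 0.05, the 12.1% and the median of 8 participants are correct for one-by-one observation, and the article does not show that they carry over to its own accrual plan. Depending on the counting convention, the false-stop rate runs from about 2-5% to about 7-18% with the 24-hour lag and 2-10 enrolments per day, with a ceiling of 32% if all of arm 1 is pending. A validation delay lowers the middle range. The abstract's limit fails above about 8.5% false stops, which some but not all of these scenarios exceed. The ranges rest on assumed accrual rates, onset times and validation delays. They do not show that the threshold or prior is wrong.

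**What to change.** 1. Reconcile the simulation description (Search for the optimised design), the timing of looks (Characteristics section and note to Table 1), the claim of flexibility (Practical implications) and the reason for rejecting frequentist monitoring (Alternative existing designs).
2. State which participants' data enter the posterior at an event-triggered look, including those still inside the two-week window, so that the simulated and applied rules are the same.
3. Re-run Tables 1 and 2 under that definition with the projected accrual, the 24-hour lag, event-onset times and the validation delay. Restate the false-stop and overall error figures, and the abstract's limit if needed.
4. Report the number of arm 1 participants already vaccinated when the rule stops, because the number counted in the posterior can be smaller.

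The cost is a sentence of definition, extra simulation work and possibly less favourable stated figures. No participants are added, and no change to the stopping threshold or to clinical management is proposed.
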